### 2.10. Ethics

The project design, procedures, and informed consent form have been approved by the Ethics Committee of the University of Milan-Bicocca and will be proposed to the Ethics Committee of the hospitals in which patients will be recruited. The language used in informed consent form and during recruitment will minimize the possibility of coercion or undue influence: patients will be clearly informed that participation in the study will be voluntary and that participation choice will not affect their healthcare process.

## 3. Discussion

This report describes the rationale, design, and methods of the TTCYB study, a randomized controlled intervention that evaluates the efficacy of a tailored print intervention to improve healthy lifestyle in four behaviors (diet, physical activity, alcohol intake, and smoking behavior). This intervention targets a vulnerable and rapidly expanding segment of the population, CVD patients. The efficacy of the intervention in the tailored group compared to the non-tailored and usual care groups will be evaluated through patients’ judgments about the materials; changes in each one of the four lifestyle behaviors considered; improvements in body mass index, systolic and diastolic blood pressure; and medication adherence. If the TTCYB is efficacious, it will have implications for the design and implementation of tailored communication programs that aim at stimulating healthy behaviors to prevent worsening in patients with chronic diseases. The anticipated strengths of the study protocol include the target population, the longitudinal design, and the analysis not only of the intervention’s efficacy but also of the possible moderators of this efficacy. Besides, the intervention suggested in this protocol uses longitudinal tailoring based on models of health behavior combined in a way that has not been tested before to the best of our knowledge. The duration of the follow-up is one year, so it will be possible to investigate the long-term effects of the intervention. This project addresses major health issues and aims to contribute to the empirical and theoretical basis for developing effective primary and secondary preventive interventions. The proposed methodology can also be applied to other health problems that can benefit from lifestyle interventions. Finally, concepts from this study can potentially be extended to the primary prevention of cardiovascular diseases among high-risk groups.

## 4. Conclusions

Several studies show that substantial reductions in the CVD risk can be obtained through lifestyle changes but data regarding the long-term effects of tailored lifestyle interventions among cardiovascular patients are still lacking.

This article describes a novel protocol, the “Time to Change Your Behavior” (TTCYB) study protocol, a theory-based, tailored print message intervention to improve cardiovascular patients’ lifestyles. The project has the potential to affect preventive health programs, given that TTCYB could be a new intervention capable of preventing clinical worsening and relapses in chronic patients. More research will be needed to determine how to integrate the protocol into routine healthcare processes.

## Figures and Tables

**Figure 1 ijerph-17-02919-f001:**
[figure not shown]
Flowchart of study participation.

**Table 1 ijerph-17-02919-t001:** Overview of measures over the different time points of the study.

	Baseline	Time 2—Six Months after Baseline	Time 3—12 Months after Baseline
Lifestyle behaviors	x	x	x
HAPA constructs	x	x	
Illness perception	x	x	
Needs for Information	x	x	
Medical adherence	x	x	
Locus of control	x	x	
Anxiety and depression	x	x	
General Self Efficacy	x	x	
Clinical evaluation	x	x	

**Table 2 ijerph-17-02919-t002:** Tailoring scheme for the development of messages related to the lifestyle.

Patients’ Intention to Change Stage	Social-Cognitive Predictor	Example of a Tailored Message
Non intender a	Outcome Expectancy	*“You reported that in changing your diet you are afraid about the difficulty to buy the right products. Don’t be afraid of this, because, especially in recent years, there is growing attention towards a healthy diet. The greater transparency that has been reached in the communication properties of the food will certainly help you to choose the best groceries. You have to always remember to BRING ON YOUR TABLE ONLY FOOD THAT ALLOWS YOU TO FEEL GOOD”.*
Non intender b	Self-Efficacy	*“When you answered the questionnaire, you declared that don’t want to change your diet because you thought you would not be able to do so. Trying to change your nutrition is not so difficult as it sounds. Try to make one change at a time; it is not necessary to change everything at once. Start, for example, by some very simple things, maybe planning the day in which to start your diet and mark it on the calendar. You can also start by searching for a nutrition specialist, who could give you important advice”.*
Preintender	Outcome Expectancy	
Intender	Action Planning	*Planning how to start changing your diet is the first step to actualize the intention to change. From the answers at the questionnaire, it emerged that you have no plan on how to manage the situation in which is difficult to maintain the change (e.g., the lunch at work). Try to organize your lunch by preparing it at home in order to avoid buying unhealthy stuff.*
Actor	Maintenance and Recovery Self-Efficacy	*Do not worry if your partner and/or your family would not change their eating habits with you. It is not necessary that everyone in the family changes habits. Probably when they will see the positive outcomes that you will achieve with your diet, they will ask you for advice and suggestion to eat like you!*

**Table 3 ijerph-17-02919-t003:** Telephone survey to collect patients’ judgments after the delivery of the material.

Questions on a Five-Point Likert Scale (1 = not at All; 2 = Few; 3 = on Average; 4 = Sufficiently; 5 = Very	Dichotomous Question (Yes/No)
The material was attractive?	Have you read the material?
The material was easy to understand?	Have you stored the material?
The material encouraged your reflection?	Have you shown the material to others?
The material increased your knowledge about hypertension?	Would you read the material again in the future?
The material was personalized on your specific situation?	Was the information in the material new?
The material contained information pertinent to your specific situation?	Do you think it would be useful to receive this kind of material again in the future?
The material was complete?	
Would you make behavioral changes based on the material (specific for diet, physical activity, alcohol intake, and smoking behavior)?

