
### The “Time to Change Your Behavior” (TTCYB) Intervention

The “Time to Change Your Behavior” (TTCYB) is a randomized controlled intervention that uses tailored health print educational material to improve healthy lifestyle behaviors (dietary behavior, physical activity, alcohol intake and smoking behavior) in patients affected by acute coronary syndrome (ACS) or essential hypertension. It is a pragmatic intervention that primes the patient to self-manage by making relevant changes in the following four behaviors: diet, physical activity, alcohol intake, and smoking. The purpose of this paper is to outline the rationale and design of the TTCYB Intervention Study. This study will provide insight into the effect of tailored print educational materials in promoting lifestyle changes among patients diagnosed with CVDs. The specific aims of the study will be
to determine whether tailored materials are perceived as more useful, understandable, and complete compared to non-tailored ones;to understand whether the TTCYB intervention is effective in promoting changes in diet, alcohol intake, physical activity, and smoking behavior among patients with CVDs;to explore the effects of the TTCYB intervention compared with two control groups (described below) on secondary endpoints, including body mass index and systolic and diastolic blood pressure;to evaluate socio-demographic and psychological factors such as self-efficacy, locus of control, and anxiety and depression, which could moderate the effectiveness of the intervention.

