### 2.3. Eligibility

All participants will have to meet the following eligibility criteria: 18 years of age or older; diagnosis of essential arterial hypertension (SBP ≥ 140 mmHg and/or DBP ≥ 90 mmHg, evaluated in the standard way or by 24-h mean arterial pressure (MAP) value monitoring) or ACS; able to complete the study measures and interventions in Italian; without other serious diseases (such as cancer) or psychiatric disorders that could compromise the participation in the study.

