#### 2.5.1. Tailored Group

Participants randomized to the tailored group will receive tailored health material about ten days following the baseline assessment.

The tailored material consists of a nine-page full-color booklet containing a set of information the patients need to know to better manage the disease. The first part of the brochure contains a set of information related to the illness (medical information on the disease and the pharmacological treatment, information on how to manage the distress and the change in life due to the illness, information on the risks and complications of CVDs); the second part is focused on the lifestyle habits (diet, physical activity, alcohol intake, and smoking behavior) that should be modified after a CVD diagnosis.

The two parts are tailored and address different variables. The first part provided personalized information on
Adherence to medical treatment. For example, if a patient answers “yes” to the question “Sometimes if you feel worse when you take the medicine, do you stop taking it?”, he/she will receive a message like “Pay attention, because the treatment for hypertension must not be interrupted without a physician’s approval”.Illness perception. For example, if a patient answers “For a very short time” to the question “How long do you think your illness will continue?”, he/she will receive a message like “Please note that acute coronary syndrome is a chronic disease; this means that it is a long-lasting condition that can be controlled but not cured and you’ll need to take pharmacological treatment for life”.

The second part will be based on
Descriptive feedback on the behavior. For example, “Based on your answers, we determined that your daily consumption of fruits and vegetables is not healthy”. Descriptive feedback is one of the effective strategies used to tailor communication [46], to stimulate patients’ self-referential thought or otherwise focusing attention on specific behaviors related to the outcome of interest.HAPA constructs. In line with HAPA, health messages will be customized to the patients’ intention to change. Specific messages will be developed to address the social-cognitive predictors emerging in the different phases. Patients will be divided into five different stages of changes:Patients who do not intend to change their behavior (non-intenders). This group will be divided into two subgroups:

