#### 2.5.2. Non-Tailored Group

The non-tailored group will complete the same questionnaire as the tailored group; participants in this group will be mailed a generic health promotion brochure promoting lifestyle changes. The generic material consists of an 8-page full-color booklet containing a generic set of information related to the illness and the lifestyle habits that should change after a diagnosis of hypertension or ACS.

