#### 2.6.3. Patients’ Judgments about the Material

About seven days after the dispatch of the material, patients in the T and NT group will receive a telephone call in which they will be asked to judge the materials. The telephone survey will consist of dichotomous and five-point Likert scale questions. Table 3 explains the multiple questions in detail.

The same procedure (health material and telephone interview) will be conducted after the six-month follow-up.

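### The survey's knowledge item and the information-needs question are printed for hypertension only, although ACS patients are also enrolled

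*Protocol article*

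**What the plan says.** The Introduction describes the trial as one "in patients affected by acute coronary syndrome (ACS) or essential hypertension". Section 2.3 (Eligibility) gives the same two routes of entry: hypertension above stated pressure limits, "evaluated in the standard way or by 24-h mean arterial pressure (MAP) value monitoring) or ACS".

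Under section 2.6.3, "patients in the T and NT group will receive a telephone call in which they will be asked to judge the materials". The usual care group is not surveyed. That section presents Table 3 as the detailed account of the questions, and the survey is repeated after the six-month follow-up. Among the five-point items Table 3 prints "The material increased your knowledge about hypertension", with no ACS variant.

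Section 2.4.7 introduces the information-needs domains as relating to either disease. It then prints the first question as being about the management of the respondent's hypertension. The second question, a ranking of the same domains, names no disease. Section 2.5 lists need for information among the constructs operationalized in the intervention.

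On the brochures, section 2.5.1 gives one tailored message that names ACS ("Please note that acute coronary syndrome is a chronic disease") and one that names hypertension ("the treatment for hypertension must not be interrupted without a physician’s approval"). Section 2.5.2 describes the generic booklet as covering "lifestyle habits that should change after a diagnosis of hypertension or ACS".

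**The concern.** An item that names hypertension does not ask an ACS patient about the disease for which he or she was enrolled. Such a patient may have learned a great deal about ACS from the brochure and have no way of saying so in answer to this item. In that subgroup the score reflects something other than knowledge gain about the patient's own disease.

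Two things are at stake. The first is the tailored versus non-tailored comparison on the knowledge item. Patients' judgments are the subject of the first aim, and both the Abstract and the Discussion list them among the ways effectiveness will be assessed. The second is the information-needs question. Its answers are described as feeding the intervention, so a misfit there would touch an input to tailoring as well as a rating.

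**Working it through.** **1. The texts side by side**

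| Place | Population or disease named |
|---|---|
| Introduction (TTCYB Intervention) and 2.3 | Hypertension or ACS |
| 2.4.7, description of the domains | Hypertension or ACS |
| 2.4.7, first question as printed | Hypertension only |
| 2.5.1, example messages | One names ACS, one names hypertension |
| 2.5.2, generic booklet | Hypertension or ACS |
| 2.6.3, who is surveyed | All tailored and non-tailored patients |
| Table 3, knowledge item | Hypertension only |

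The two printed items are narrower than the population that answers them. In 2.4.7 the mismatch lies within a single section.

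**2. What the mismatch does to the arm comparison**

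Let δ be the true tailored minus non-tailored difference in own-disease knowledge gain, p the share of ACS patients, and b the amount by which the wording lowers that difference among ACS patients. Then

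observed difference = δ − p × b.

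The article gives none of δ, p and b. The sign of b depends on how much hypertension content an ACS patient meets in each brochure:

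- b = 0: the wording shifts both arms equally, so there is no distortion.
- b = δ: the item is uninformative for ACS patients in both arms. The observed difference is δ(1 − p), which is dilution toward zero.
- b > δ: ACS patients favour the generic booklet on this item. The overall sign reverses only if p × b > δ.
- b < 0: the difference is inflated in favour of tailoring.

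**3. Illustration, on assumed inputs only**

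No figure in the plan bears on this item. The stated sample size supplies only an arm size. It reproduces: with f = 0.10, three groups, three measurements and correlation 0.5, λ = 0.10² × 204 × 3 / (1 − 0.5) = 12.24, with 4 and 402 degrees of freedom, and power is 0.806. The smallest N reaching 0.80 is 202, which rounds up to 204 for equal groups, or 204 / 3 = 68 per arm.

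Assume SD 1, δ = 0.5, no losses, and two-sided α of 0.05. The standard error is √(2/68) = 0.171, and power is approximately Φ(difference / 0.171 − 1.96).

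| Assumed ACS share | b = 0 | b = 0.5 (uninformative in both arms) | b = −0.5 |
|---|---|---|---|
| 25% | 0.5 (power 0.83) | 0.375 (0.59) | 0.625 (0.95) |
| 50% | 0.5 (0.83) | 0.25 (0.31) | 0.75 (0.99) |
| 75% | 0.5 (0.83) | 0.125 (0.11) | 0.875 (>0.99) |

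The table shows that the same printed wording is compatible with no effect, dilution or inflation. It does not estimate the bias in this trial.

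**4. Reach**

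Table 3 has eight five-point items and six yes/no items, so one of 14 is affected. Section 2.9 describes t-tests and chi-square tests for the judgments and mentions no composite score, so the misfit is not shown to carry into other items. Section 2.6.1 makes behavior change the primary outcome, which this item does not enter.

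**The case against.** **The printed line may be the hypertension version of a two-version form.** Section 2.4.7 speaks of both diseases and then prints a question for one, and 2.5.1 alternates its examples. The authors may be illustrating with hypertension wording, and an article condenses the full script. This is a fair possibility, but nothing in the article says that an ACS version exists, and 2.6.3 offers Table 3 as the detailed list. It therefore supports the second branch of the fix (state that such versions are used) and does not remove the point.

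**A reader might infer a bias against tailoring.** On that reading, ACS patients with an ACS-specific tailored brochure must answer at the bottom of the scale, while ACS patients with the generic booklet answer higher. The documents do not support this. It needs an ACS tailored brochure without hypertension content and a single generic booklet that carries it. Neither is stated. Section 2.5.1 says the tailored brochure also covers cardiovascular risks and complications in general. The wording of 2.5.2 fits one booklet or two. Eligibility does not exclude patients with both diagnoses, so even a low score from ACS patients is not assured.

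**The item carries little weight.** This stands. The first aim concerns usefulness, comprehension and completeness. Table 3 covers comprehension, completeness, personalization, pertinence and novelty of the information in wording that names no disease.

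**Conclusion.** The mismatch between items and population is real and is visible in the printed text. As printed, the Table 3 knowledge item and the first question of 2.4.7 do not measure knowledge gain or information need about the patient's own disease in ACS patients. The comparison of the tailored and non-tailored arms on the knowledge item is at least potentially diluted. The direction of any bias between arms is undetermined, and no size can be given, because the ACS share, the brochure contents and ACS patients' responses to the item are not in the article.

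For the information-needs question, the consequence for tailoring cannot be sized either: 2.5 names the construct, but 2.5.1 shows no message driven by it.

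Severity is minor, and the primary outcome is unaffected. The conclusion assumes that the printed wording is used for all surveyed patients; if diagnosis-specific forms are already in use, only the reporting needs correcting.

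**What to change.** Word both items for the enrolling diagnosis. In Table 3, ask whether the material increased knowledge about *your condition (hypertension / acute coronary syndrome)*, with the interviewer reading out the one that applies. Make the same substitution in the first information-needs question of 2.4.7. If diagnosis-specific versions already exist, state in 2.4.7 and in Table 3 that they are used.

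The cost is a one-line change to the telephone script and to the questionnaire, or one sentence in each place. Design, sample size and analysis stay as they are.
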